### Procedures

Participants will be recruited either while they are in the hospital for transplant surgery, or if that is inconvenient, during their first clinic visit following transplant surgery. After informed consent is obtained, demographic and clinical data will be collected by self-report and by medical record audit. At the time of each EMB, data from the medical record will be abstracted to confirm current medications, serum levels of anti-rejection medications, clinical data regarding EMB results, and other clinical data reflecting myocardial performance consistent with rejection status. Only one anti-rejection medication (tacrolimus) is associated with an increased QT interval. If a patient is on chronic tacrolimus therapy without a change in dosage, it should not interfere with the daily ECG monitoring measurement because we will be comparing each patient with him/herself and noting any change from the previous day's QT interval. However, we will track initiation or change in any QT-prolonging drug. On their website, the Arizona Center for Education and Research on Therapeutics [15] maintains a comprehensive list of QT- prolonging drugs that we have incorporated into the medications section of our electronic database system. Further, on a quarterly basis, we will continue to reference this website for new drugs as they come to market and update our data capture to include those associated with QT-prolongation.

The other drug class that patients may be taking is 3-Hydroxy-3-Methyl-Glutaryl Coenzyme A Reductase inhibitors (i.e., statins) which are known to shorten the QT interval. Thus, we will also monitor statin therapy. To insure patient safety, we will notify patients' transplant cardiologists within 48 h of the detection of any QTc interval exceeding the population 99th percentile for adult males (> 470 ms) or females (> 480 ms) [16].

At the time of informed consent and enrollment, subjects will receive the HeartView™ recorder and its companion Internet Transmitter, which will transmit the subject's ECG as described earlier. Subjects will be asked to record a 10-s 8-lead ECG daily for 6 months.

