### Analysis of ECG monitoring data

The ECG will be sent to a large server hosted by the UCSF Office of Academic and Administrative Information Systems (OAAIS). The server is a secure, highly redundant data center with 24/7 availability due to back-up generators that protect against power outages. The system provides nightly data backup. Investigators in the [name] Lab will access the ECG data by logging on with a username and password via a Virtual Private Network (VPN), which encapsulates data transfers between networked devices not on the same private network and keeps the transferred data private from other devices. Investigators who analyze the daily ECG data will be blinded from all information regarding the subject's clinical status and biopsy results. In addition, pathologists who grade the biopsies and clinicians who provide medical care in the transplant clinics will be blinded from the QT interval monitoring data.

QT and RR intervals will be made in a computer-assisted manner. The Aerotel measurement software provides a zooming feature to enlarge ECG waveforms for better visualization. In addition, electronic calipers are provided so that the researcher will select the appropriate waveform onset and offset points and the computer software will provide the interval value in milliseconds (ms). The QT interval will be measured from the onset of the QRS waveform to the end of the T waveThe end of the T wave will be defined as the intersection of a tangent to the steepest slope of the last limb of the T wave and the baseline (Figure 2) [18]. A standardized correction to account for the effect of HR will be applied (QT_C_). An increase in the QT_C _interval from the previous day of at least 25 ms that persists for 3 consecutive days will be considered abnormal [10].

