### Statistical analysis

Using the variable definitions in Table 2, a logistic regression analysis will be performed with the independent variable being presence/absence of the ECG criteria (ΔQT_C _≥ +25 ms × 3 days [10]) and the dependent variable being presence/absence of acute allograft rejection. Odds ratios and confidence intervals will be reported as well as the universal proportions used to determine the value of new diagnostic criteria (sensitivity, specificity, positive/negative predictive value, and predictive accuracy, Table 3).

**Table 2 T2:** Variable definitions for statistical analysis

Variable	Definition	Type of Variable
ΔQT_C_	≥ +25 ms increase in QT_C _interval from previous day lasting 3 consecutive days [10]	Continuous (expected range, 10-100 ms)

Acute allograft rejection	EMB category 1R or 2R or 3R with confirmation by treating physician	Categorical; dichotomous (yes/no) No = 0; Yes = 1R or 2R or 3R

Days to rejection	Number of days from first positive ECG criterion to mild, moderate, or severe rejection diagnosis. If the ECG criterion follows rejection, a negative # of days will be reported.	Continuous (expected range -365 to +365)

Acute rejection severity	EMB category: 1R (mild), 2R (moderate), 3R (severe)	Categorical

Cardiac rhythm	Sinus rhythm, atrial fibrillation, atrial flutter, junctional rhythm	Categorical

Heart rate	Heart rate per minute calculated from 30 s rhythm strip	Continuous (expected range, 60-120)

P wave duration	Interval from beginning to end of P wave in ms (measure of intra-atrial conduction delay)	Continuous (expected range, 70-126 ms)

QRS duration	Interval from beginning to end of the QRS waveform	Continuous (expected range, 72-160 ms)

PR interval	Interval from the beginning of the P wave to the beginning of the QRS complex measured in ms. PR interval > 200 ms indicates an abnormal delay of conduction (1^st ^degree AV block).	Continuous (expected range, 112-240 ms)

QRS amplitude	Height of QRS waveform in μV	Continuous (expected range, 500-1000 μV

T_PEAK _- T_END_	Interval from the peak of the T wave (or nadir in inverted T waves) to the end of the T wave in ms. Prolonged T_PEAK _-T_END _indicates heterogeneity of repolarization and risk for arrhythmia	Continuous (expected range, 112-240 ms)

**Table 3 T3:** Definitions of Universal Proportions

Criterion	Definition
Sensitivity	Proportion of those with acute rejection who are positive for the ECG criterion

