Specificity	Proportion of those without rejection who are negative for the ECG criterion

Positive Predictive Value	Proportion of patients with positive ECG criterion who have rejection

Negative Predictive Value	Proportion of patients with negative ECG criterion who do not have rejection

Predictive Accuracy	$\frac{\#\text{true positives}\pm \text{true negatives by the ECG criterion}}{\text{Total }\#\text{ of patients enrolled in the study }\times \text{ 1}00}$

Descriptive statistics (means ± SD) will be used to describe the average time period between the development of the ECG criterion and biopsy evidence of rejection. In addition, we will report the proportion of subjects who develop the ECG criterion (≥ +25 ms increase in QT interval from previous day lasting 3 consecutive days [10]) before, during, or after the stages of mild, moderate, and severe rejection.

The Kaplan-Meier method with the log-rank test will be used to estimate survival curves over one year and to compare all-cause mortality in patients who are positive or negative for the QT_C _criterion. Cox Proportional Hazard modeling will be used to control for baseline differences between groups and for tacrolimus use.

Logistic regression will be used with the dependent variables of rejection (yes/no) and all- cause mortality (yes/no). In both regressions, tacrolimus dosage (with "0" entered if the patient is not receiving tacrolimus) will be included as a covariate in the model. If any of the explorative variables are statistically significant, a multiple logistic regression model will be used including the ECG criterion of interest to determine whether additional ECG criteria are independent predictors of rejection and death.

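### The ECG criterion cannot tolerate a missed recording at the onset of a rise, so sensitivity and NPV partly measure recording adherence

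*Protocol article*

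**What the plan says.** Under Analysis of ECG monitoring data, an increase in QTc "from the previous day of at least 25 ms that persists for 3 consecutive days" is abnormal. Table 2 repeats the rule as a rise in the "interval from previous day lasting 3 consecutive days". The Procedures section confirms that each patient's own QT interval on the preceding day is the comparator.

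On data collection, the Procedures section states: "Subjects will be asked to record a 10-s 8-lead ECG daily for 6 months".

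On analysis, the Statistical analysis section enters the test into logistic regression as "presence/absence of the ECG criteria". Table 3 defines sensitivity as "Proportion of those with acute rejection who are positive for the ECG criterion" and specificity as "Proportion of those without rejection who are negative for the ECG criterion". Predictive accuracy is divided by the total number "of patients enrolled in the study".

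The only statement on completeness, under Follow-up and end-points, concerns rejection and death. It does not concern the daily ECG.

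**The concern.** A sustained rise has one onset, and the rule can recognise it only there.

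- If the day before onset is missing, the first raised day has no comparator, and later days are compared with a value that is already raised.
- If the first raised day is missing, the second has no previous-day value.
- If the second or third raised day is missing, the run is no longer consecutive.

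In each case the episode fails the criterion however long the rise lasts. The difficulty therefore lies in the reference point and run length that the article fixes. A general missing-data policy would not remove it.

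The result has two states, and every enrolled patient is in the accuracy denominator. An episode that could not be assessed therefore has nowhere to go except, most naturally, absent. Sensitivity belongs to the first primary aim. A marker that tracks rejection well could be reported as insensitive because patients missed recordings.

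**Working it through.** The article gives no adherence rate and no missing-day figure, so there is no stated number to reproduce. The adherence values below are assumptions, shown as a range.

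**1. How much of the 6 months a gap removes.** Take 6 months as 182 daily recordings. Possible four-day windows: 182 − 3 = 179.

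- One missed day removes 4 windows: 175/179 = 97.8% remain.
- A 16-day gap (the median rehospitalization stay cited in the Background) removes 16 + 3 = 19: 160/179 = 89.4% remain.
- With independent daily recording, the chance of no complete four-day run anywhere in 182 days is about 4 × 10⁻¹⁸ at adherence 0.80 and 0.13% at 0.50.

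So gaps do not stop a patient from ever meeting the criterion. What matters is whether a gap falls on the onset.

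**2. Chance that one particular onset can be assessed.** With independent daily recording probability p, all four required days are present with probability p⁴.

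**3. Effect if unassessable onsets count as absent.** For illustration, take the 77% sensitivity and 96% specificity listed in Table 1 for a rise of more than 25 ms in the 200-patient study. Allow each patient one relevant episode. Then observed sensitivity = 0.77 × p⁴ and observed specificity = 1 − 0.04 × p⁴.

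| Adherence p | p⁴ | Sensitivity | Specificity |
|---|---|---|---|
| 0.99 | 0.961 | 74.0% | 96.2% |
| 0.95 | 0.815 | 62.7% | 96.7% |
| 0.90 | 0.656 | 50.5% | 97.4% |
| 0.80 | 0.410 | 31.5% | 98.4% |

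**4. Effect on NPV.** NPV = Sp(1 − π) / [Sp(1 − π) + (1 − Se)π], with π the rejection rate. The article cites 25 to 35% in the first 6 months.

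- π = 0.25, complete recording: 0.720 / (0.720 + 0.0575) = 92.6%. At p = 0.90: 0.7303 / (0.7303 + 0.1237) = 85.5%.
- π = 0.35, complete recording: 0.624 / (0.624 + 0.0805) = 88.6%. At p = 0.90: 0.6329 / (0.6329 + 0.1732) = 78.5%.

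**5. What tolerance of gaps recovers.** Suppose the last available ECG before the rise is the reference and any 3 consecutive recorded days within the rise suffice. For a rise lasting 7 days, capture is 99.2%, 96.7% and 86.9% at p = 0.95, 0.90 and 0.80, against 81.5%, 65.6% and 41.0% under the literal rule. For a rise lasting only 3 days the gain is small: capture is p³ = 85.7%, 72.9% and 51.2%.

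**The case against.** The strongest reply is that this is missing-data handling, which a condensed article may leave to a full protocol or analysis plan, and that nothing in the text says a gap is scored negative. The second part is right: counting such episodes as absent is inferred from the two-state coding and the all-enrolled denominator, and every sensitivity and specificity table has two states. The silence on missed days would not by itself be a finding. What survives is that the article does fix the previous-day reference and the three-consecutive-day run, and these fail at a gap whatever is decided later about missing data.

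A reader might go further and infer that any missed day or hospital stay makes the criterion unmeetable for the patient. The documents do not support that. A gap blocks only the windows it overlaps, and the patient can turn positive at other times.

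A reader might also infer that rehospitalization causes gaps around rejection. The Background does name rejection as the commonest reason for readmission and cites 64% rehospitalized. But that is a one-year figure with no timing relative to rejection, and nothing says recording stops in hospital. The device may be issued there and transmits over the mobile network. The article also provides training, caregiver involvement and staff monitoring of transmissions. Clustering of gaps around rejection is plausible but not stated.

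Finally, the 77% and 96% come from a study with two ECGs per subject and do not describe the three-day rule. Multiplying by p⁴ gives each patient a single chance, whereas Table 3 scores patients over the whole period. The table shows direction and sensitivity to adherence. It does not predict results.

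**Conclusion.** The point holds at the level of the episode. Followed literally, the criterion requires four consecutive daily ECGs around an onset, and a missed recording on any of them prevents that rise from being recognised. If such episodes are counted as absent, as the coding most naturally implies, sensitivity and NPV fall with adherence and specificity rises slightly: from 96% to 97.4% at adherence 0.90 in the illustration, against a fall in sensitivity from 77% to 50.5%.

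The actual size cannot be derived from the article. The illustration assumes independent daily recording, one relevant episode per patient and borrowed accuracy figures. Gaps that cluster around illness, or several episodes in one patient, would change it. The criterion should be amended because it bears on the first primary aim and the change is cheap.

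**What to change.** Keep the 25 ms threshold and three recordings, but apply them to available recordings:

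- take as reference the last available recording within a short prespecified window before the rise;
- require 3 successive available recordings at least 25 ms above it, within a prespecified number of days;
- classify a period around a biopsy with too few recordings as non-evaluable rather than negative, and report how often this happens by rejection status;
- report the literal four-calendar-day rule, with gaps counted as negative, alongside.

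A longer baseline, such as the median of the preceding week, would be a different index test that could also flag gradual drift. It is not needed to cure this defect.

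The change needs wording and programming on recordings that the study collects anyway. The downside is small: two versions of the accuracy estimates must be reported, and the window lengths must be fixed before the blinded ECG readings are linked to biopsy results.

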**Figure 2 F2:**
[figure not shown]
**Measurement of QT Interval**. A tangent is drawn to the steepest slope of the last limb of the T wave; the end of the T wave is the intersection of this tangent with the baseline.

To explore the potential diagnostic and prognostic value of additional ECG measurements, the following variables will also be measured on the daily ECG recordings: cardiac rhythm, heart rate, P wave and QRS duration, PR interval, QRS amplitude, and the interval from the peak of the T wave to the end of the T wave [19]. A prolonged T_PEAK _- T_END _interval is thought to represent heterogeneity of ventricular repolarization across the 3 layers of the myocardial wall [20] and has been associated with risk for sudden cardiac death from torsades de pointes [21].

### Diagnosis of acute allograft rejection

Rates of acute allograft rejection have varied, but the most recent rates of rejection in the first 6 months after transplant are reported to be 25 to 35% [2]. The diagnosis of acute allograft rejection is made by an EMB which will be performed in the hospital cardiac catheterization laboratory at each site. Generally, 3-6 biopsy specimens of the right ventricular endocardium are taken to minimize false negative tests. Each site will follow its own acute rejection surveillance protocol. In general, these protocols require weekly or biweekly EMBs during the first two to three post-transplant months. After that time, biopsies are performed less frequently, based on clinical judgment and risk of rejection. At each site, EMBs will be graded by clinical pathologists experienced with the heart transplant population and using the International Society of Heart and Lung Transplantation standards for acute rejection. Although early reports indicated inter-operator variability in the interpretation of EMB results [22], the use of the standardized grading system has improved the reliability and validity of the measurement. Current variability in interpretation of biopsy results occurs mainly in the diagnosis of Grade 2 rejection by local pathologists which may be misinterpreted in the presence of endocardial infiltrates called Quilty lesions [23,24]. To control for potential variability, we will monitor and record clinical and hemodynamic indicators of myocardial performance, which are obtained at the time of each biopsy or at regular clinical assessments, to support the biopsy interpretation, particularly regarding Grade 2 rejection. Such a multi-factorial approach to identification of rejection has been recommended [24].

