## Background

The prevalence of American adults living with a heart transplant was 20,369 in 2009, the most recent year for which complete data are available [1]. Acute allograft rejection is a major cause of early mortality, a rate that reaches 13% in the first year after heart transplantation in adults [1,2]. According to the 2011 annual United States data published from the International Society for Heart Lung Transplantation Registry, 26% of heart transplant recipients have at least one rejection episode within the first year following transplant surgery [2]. Acute rejection remains the most common cause of morbidity and rehospitalization. Jalowiec [3] reported that 64% of heart transplant recipients were rehospitalized during the first year after transplant surgery (median length of stay, 16 days), and 37% were rehospitalized more than once. Rejection is also a primary cause of urgent re-transplantation, a situation that is perceived by some to be morally unfair because these patients are allowed a second transplant while others are waiting and often dying before receiving their first transplant. Thus, the financial, physical, and emotional toll associated with acute rejection is significant.

In order to detect the early stages of rejection so that more aggressive and early immunosuppressant therapy can be initiated, frequent biopsies of heart tissue are performed (typically, weekly or every other week in the first three months and then monthly or every other month during the first year). Although endomyocardial biopsy (EMB) is not a perfect "gold standard" for a correct diagnosis of acute allograft rejection, it is considered the best available test and thus, it is the current standard practice. Unfortunately, EMB is an invasive and costly procedure that is not without risk [4,5]. If a simple noninvasive biomarker could be identified to detect the early stages of acute rejection, it might be possible to reduce the number of invasive biopsy procedures and to initiate earlier therapy that might prevent death from severe rejection.

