### Sample

A sample of 325 adult heart transplant recipients will be recruited from the Columbia University-New York Presbyterian Medical Center (CU-NYP), the University of California, Los Angeles (UCLA), and Cedars Sinai Medical Center (CSMC) in Los Angeles, CA. Respectively, demographic characteristics at these sites are: male (68.9%, 75.7%, and 79.7%); White (53.1%, 59.1%, 73.4%); Black (20.3%, 9.4%,12.5%); Latino (14.5%, 19.9%, 9.4%) and Asian (11.3%, 10.5%, 3.1%) [1]. Inclusion criteria are: 1) ≥ 18 years of age, 2) first heart transplant surgery within six weeks of their transplant surgery, 3) not enrolled in other research studies that conflict with the study design, 4) clinically stable at time of enrollment (i.e. no clinical symptoms of allograft impairment with ejection fraction ≥ 45%).

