### Follow-up and end-points

The number and grade of acute allograft rejection episodes will be collected for a period of one year following transplant surgery. Data on all-cause mortality within the first year will be collected. Because all transplant centers are required to report their data to the transplant registry, we anticipate no loss to follow-up or missing data regarding rejection or death.

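### Biopsy becomes irregular and risk-driven after months two to three, but rejection is coded yes/no with no unverified class and no alarm-to-biopsy window, so accuracy may be biased in either direction

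*Protocol article*

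**What the plan says.** **Reference standard.** Endomyocardial biopsy (EMB) diagnoses rejection. Under Diagnosis of acute allograft rejection, "Each site will follow its own acute rejection surveillance protocol". The same section describes the usual early pattern across sites: "these protocols require weekly or biweekly EMBs during the first two to three post-transplant months". For the later period it states: "After that time, biopsies are performed less frequently, based on clinical judgment and risk of rejection". The Background describes typical practice differently: "weekly or every other week in the first three months and then monthly or every other month during the first year".

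**ECG monitoring.** Enrolment is open for "first heart transplant surgery within six weeks of their transplant surgery" (Sample). The device is handed over at enrolment, and "Subjects will be asked to record a 10-s 8-lead ECG daily for 6 months" (Procedures).

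**Coding and accuracy measures.** Table 2 makes rejection a yes/no variable: yes is grade 1R, 2R or 3R confirmed by the treating physician, and no is coded 0. Table 3 defines specificity as "Proportion of those without rejection who are negative for the ECG criterion", and the predictive values are also proportions of patients. Days from the first positive ECG criterion to rejection may range from -365 to +365.

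**Completeness.** Rejection is collected for one year. Because centres must report to the transplant registry, "we anticipate no loss to follow-up or missing data regarding rejection or death" (Follow-up and end-points).

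**Blinding.** Treating clinicians and pathologists are blinded to the QT data (Analysis of ECG monitoring data). However, the transplant cardiologist is told within 48 hours of a QTc above 470 ms in men or 480 ms in women (Procedures).

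**The concern.** The first primary aim is the sensitivity and specificity of the ECG criterion. That needs a reference result for each patient that is reasonably complete and obtained independently of the marker. Three features work against this.

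1. After the dense phase, whether a patient is biopsied depends partly on perceived risk. With no unverified class, a patient whose rejection is never sampled becomes a non-rejector. If the ECG alarm was positive, a correct alarm is scored as a false positive. If it was negative, a miss is scored as a true negative.
2. No window ties the alarm to a biopsy. An alarm months away from a confirmed rejection, before or after it, is still a true positive at patient level.
3. The 48-hour notification can tell the cardiologist about a long QTc, so the index measurement may itself prompt biopsies despite the blinding.

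The registry argument shows that rejections which were found will be reported. It does not show that all rejections were found. The study is meant to support fewer surveillance biopsies, and accuracy against biopsies done on suspicion does not answer that question directly.

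**Working it through.** The protocol article gives 325 patients but no target accuracy or precision, so there is no stated figure to reproduce.

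**Step 1. Share of ECG monitoring after the dense phase.** Inputs: dense phase ends at D = 2 or 3 months after transplant; enrolment at e = 0 to 6 weeks; monitoring lasts 6 months from enrolment. With 30.44 days per month, 6 weeks is 42/30.44 = 1.38 months.

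Share = 1 - (D - e)/6

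- e = 0, D = 3: 1 - 3/6 = 50%
- e = 0, D = 2: 1 - 2/6 = 67%
- e = 2 weeks (0.46 months): 58% (D = 3) to 74% (D = 2)
- e = 6 weeks, D = 3: 1 - 1.62/6 = 73%
- e = 6 weeks, D = 2: 1 - 0.62/6 = 90%

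If monitoring stopped six months after transplant instead, the range would be 50% to 87%.

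**Step 2. Effect of unconfirmed rejections on the patient-level table.** Inputs: N = 325; sensitivity Se = 77% and specificity Sp = 96%, from the cited study of a rise above 25 ms (Table 1); true rejection rate p = 30%, the middle of the reported 25% to 35%. Treating that reported rate as the true rate is an assumption. The share d of rejecting patients ever confirmed by EMB is not in the document and is also assumed. Confirmation is taken as independent of the ECG result.

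- Apparent specificity = [(1-p)Sp + p(1-d)(1-Se)] / [(1-p) + p(1-d)]
- Apparent PPV = p·d·Se / [p·Se + (1-p)(1-Sp)]
- Apparent NPV = [(1-p)Sp + p(1-d)(1-Se)] / [(1-p)Sp + p(1-Se)]
- Correct alarms scored as false positives = 325·p·(1-d)·Se

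For d = 0.8:

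- specificity = (0.672 + 0.0138)/0.76 = 90.2%
- PPV = 0.1848/0.259 = 71.4%
- NPV = 0.6858/0.741 = 92.6%
- rescored alarms = 325 × 0.30 × 0.20 × 0.77 = 15.0

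| d (assumed) | Specificity | PPV | NPV | Correct alarms scored as false positives |
|---|---|---|---|---|
| 1.0 | 96.0% | 89.2% | 90.7% | 0 |
| 0.9 | 93.0% | 80.3% | 91.6% | 7.5 |
| 0.8 | 90.2% | 71.4% | 92.6% | 15.0 |
| 0.7 | 87.7% | 62.4% | 93.5% | 22.5 |

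Genuine false positives number 325 × 0.70 × 0.04 = 9.1, so a modest number of unconfirmed rejections can match or exceed them. At d = 0.8 with p from 25% to 35%, specificity runs from 91.4% to 88.9% and PPV from 69.2% to 73.0%. Sensitivity stays at 77% in this model only because confirmation is assumed independent of the ECG.

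**Step 3. The opposite error.** The missing window credits alarms unrelated in time to a confirmed rejection. The document gives no alarm rate over time, so this cannot be sized. It flatters the marker.

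**Step 4. ECG time that a window would keep.** With a 14-day window (an example) and late biopsies 30 to 60 days apart (the Background's monthly or every other month), the verified share of late ECG time is 14/30 = 47% to 14/60 = 23%. So 53% to 77% of it would be unverified.

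**The case against.** The strongest reply is that Table 3 counts patients. No unbiopsied stretch of time is ever labelled negative, and a patient with any confirmed rejection within the year is a rejector, so an alarm in that patient is a true positive. Only patients whose rejection is never confirmed are misplaced, and someone caught in the weekly or biweekly phase is already classed as a rejector. This stands. A reader might infer that early alarms in general will be scored as false positives, and the document does not support that.

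Second, the Background's monthly or every-other-month pattern suggests that late biopsy is largely routine, which would weaken the risk-driven argument. That also has force. But the Diagnosis section says otherwise and leaves the schedule to each site, so the two descriptions must be reconciled.

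Third, 50% to 90% is a share of ECG days, not of rejections, whose timing within the six months is not given. The upper end needs enrolment on the last eligible day, while recruitment is planned in hospital or at the first clinic visit. It shows exposure, not bias.

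Fourth, blinding of clinicians limits how far biopsy can depend on the ECG. It does, except through the 48-hour notification.

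Finally, an article may leave rules for verified negatives to the full protocol or analysis plan, and the statement on missing data can be read as being about reporting only. The first part is fair. But the yes/no coding and the expectation of no missing rejection data are stated outright, and the latter should say which kind of completeness it means.

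**Conclusion.** The concern holds in a limited form. At least half of the ECG monitoring (50% to 90%) falls where biopsy is less frequent and depends on judgment, and the outcome coding has neither an unverified class nor a link in time between alarm and biopsy. Rejections never confirmed by biopsy lower apparent specificity and PPV and raise NPV; the absent window works in the marker's favour; and the notification rule may affect sensitivity by prompting biopsies. The net direction and size cannot be derived from the document.

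The falls in specificity to about 93% to 88% and in PPV to about 80% to 62% are hypothetical. They rest on an assumed 10% to 30% of rejecting patients going unconfirmed, a 30% true rate, accuracy borrowed from one cited study, and confirmation independent of the ECG. A reader might take them as the expected loss, or conclude that the criterion will look worse than it is; neither follows. The point merits a change because it touches the first primary aim and the remedy needs no extra biopsies.

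**What to change.** - Add a biopsy-linked accuracy analysis. For each EMB, compare the ECG criterion in a fixed, pre-specified window before it with that EMB's result, allowing for clustering by patient. Class ECG time with no biopsy in the window as unverified, not negative.
- In the data already abstracted at each EMB, record whether the biopsy was scheduled or for cause, including after a QTc notification, and report accuracy separately for the two.
- Keep the patient-level Table 3 figures as a secondary result.
- Reword Follow-up and end-points so that the statement covers complete reporting of detected rejections only.
- Reconcile the Background and Diagnosis descriptions of biopsy after the early months.

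**Cost.** One added form field, a clustered analysis in addition to the patient-level one, and a wider interval, since roughly half or more of late-phase ECG time would leave the verified analysis with a 14-day window. Making scheduled biopsies the only headline result is a further step with a real trade-off, because it would move for-cause rejections out of the main estimate. It is not needed to resolve this point.
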